# A risk assessment model for chronic ankle instability: indications for early surgical treatment? An observational prospective cohort – study protocol

**DOI:** 10.1186/s12891-018-2124-5

**Published:** 2018-07-18

**Keywords:** Chronic instability, Ankle sprain, Prognosis, Ankle geometry, Model methodology

## Abstract

**Background:**

Chronic ankle instability (CAI) is a common result of an ankle sprain. Even though early surgical treatment yields the best results, overall only professional athletes are eligible for acute surgical stabilization. Treating all patients with early surgical stabilization leads to a high amount of unnecessary invasive interventions, as not all patients progress to CAI. If patients at risk of developing CAI can be identified, treatment policies may be applied more effectively and efficiently. The purpose of this study is to develop a risk assessment model to identify patients at risk for CAI that should receive early surgical treatment.

**Methods:**

In this observational prospective cohort, all patients aged sixteen years and older, reporting at the emergency department of one of the participating hospitals after sustaining a lateral ankle sprain, and filled out 1 out of 3 follow-up questionnaires and the 1 year follow-up are included. A lateral and anteroposterior radiograph is made. Patients are excluded if a fracture or other pathology is present. The included patients receive four questionnaires, including questions focusing on the sprain, treatment and complaints, the Foot and Ankle Outcome Score and the Cumberland Ankle Instability Tool. A total of eleven radiographic variables are assessed for inter- and intra-observer reliability. Additionally, four factors extracted from the questionnaires, will be evaluated for correlation with CAI. Significantly correlating factors (e.a. risk factors) will be implemented in a risk assessment model. For the final model, based on sixteen variables with a minimum of 20 events per variable and a prevalence of 30–40% after an initial sprain, a sample size of 2370 patients is needed to perform both internal and external model validation.

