### Aim of the study

To identify which patient characteristics and joint geometric factors are associated with development of CAI after an ankle sprain and subsequently develop and validate a risk assessment model to indicate which patients are at risk for developing CAI.

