#### Prognostic value of variables

To determine whether the variables, selected from current literature, can be implemented in our model, it has to be determined whether they are of prognostic value on the progression of an ankle sprain to CAI. This will be done by determining whether they have an individual correlation with instability 12 months after an ankle sprain and whether this correlation is influenced using a multivariate analysis. In case of no existing correlation, factors are left out of the model and the sample size is recalculated accordingly.

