#### Assessment of agreement

Assessment of the prognostic value of the fourteen variables will be performed on the sample size of the internal validation [36]. To avoid overfitting, the prognostic value of these 16 variables will be assessed when 10 events per variable (EPV) is reached [37]. With a maximum of sixteen variables with a minimum of 10 events per variable, a prevalence of 30–40% after an initial sprain, including a 10% loss-to-follow-up, a sample size of 593 patients is needed to assess their prognostic value (Table 2).

**Table 2 Tab2:** Sample Size calculation prognostic value, internal validation [38, 39]

EPV = no. of events/no. of regression coefficients		
Minimal EPV	≥10 Prognostic Value	≥20 Prediction Model
Change of developing CAI	30–40%	30–40%
No. of regression coefficients	16	16
(? = no of events needed)	10 =?/16 ? = 160 minimal 160 events	20 =?/16 ? = 320 → minimal 320 events
In case of 30% chance of developing CAI	160*3.33 = 532.8 patients	320*3.33 = 1065.6 patients
In case of 40% chance of developing CAI	160*2.5 = 400 patients	320*2.5 = 800 patients
Sample Size (incl. 10% loss to follow-up)	445–593 patients	889–1185 patients

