### Data analysis and statistics

Demographics of the study population will be analyzed using the descriptive statistics. All statistics will be performed with SPSS version 23.0 (SPSS Inc., Chicago, IL, USA) and R package ‘Stats’ version 3.3.3 (University of Auckland, Auckland, New Zealand). A *p*-value of < 0.05 is considered significant. Normality of data will be assessed using the Shapiro-Wilks test.

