#### Prognostic value of variables

Depending on normality of data the Pearson or Spearman correlation coefficients will be used to assess correlations. A scatterplot for numerical data and Odds Ratio (OR) for binary data will be used to provide additional information on possible correlations in the data between prognostic factors. In case of correlations (*p* < 0.10 to avoid overfitting [40]) shown by an univariate analysis, a multivariate logistic regression will be performed to assess dependency between variables. The R^2^ will be used to visualize model fitness for the contribution of a factor to the progression to CAI and for the full model.

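### Up to 16 candidates are screened and significant ones called risk factors, with no multiplicity control and no single-factor check in the second sample, so a false risk factor is more likely than the per-test level suggests

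*Protocol article*

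**What the plan says.** All references are to the protocol article.

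- **Aim of the study.** The first half of the aim is "To identify which patient characteristics and joint geometric factors are associated with development of CAI after an ankle sprain". Developing and validating the model comes second.
- **Abstract, Methods.** "Significantly correlating factors (e.a. risk factors) will be implemented in a risk assessment model". A significant correlation is thus equated with being a risk factor.
- **Analyses, Prognostic value of variables.** Each variable is assessed for "individual correlation with instability 12 months after an ankle sprain and whether this correlation is influenced using a multivariate analysis". There are two steps, one univariate and one multivariable.
- **Data analysis and statistics.** The general rule is "A *p*-value of < 0.05 is considered significant". The subsection on prognostic value uses another level for the screen: "< 0.10 to avoid overfitting [40]) shown by an univariate analysis, a multivariate logistic regression will be performed to assess dependency between variables". No level is given for keeping a variable after that regression.
- **Sample size calculation, Assessment of agreement.** "With a maximum of sixteen variables with a minimum of 10 events per variable". The text elsewhere also counts fourteen.
- **Clinical outcome measures.** All candidates are said to have earlier evidence of a link with ankle instability except MDTA, MMHA and TCA, which are to be explored.
- **Data analysis and statistics, Prognostic model.** The temporally separate second sample is used for sensitivity, specificity and the ROC curve of the model. No estimate for an individual factor is planned there.

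**The concern.** A screening p-value is a workable way to choose inputs for a prediction model. It is weaker support for a statement that one particular feature of bone geometry is a risk factor for CAI, and the first aim and the abstract invite that statement.

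With up to 16 candidates and no ranking, adjustment or exploratory label for the set, the chance that at least one named factor is false exceeds the level of any single test. The planned safeguards do not address this. The bootstrap concerns bias in the coefficients, and temporal validation concerns the model as a whole. A model can discriminate well in the second sample while one of its factors contributes nothing.

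Single factors also carry some weight later: variables with a significant correlation are to be turned into yes/no items for daily practice.

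**Working it through.** **Inputs from the protocol article:** 16 candidates at most; general level 0.05; univariate screen 0.10; CAI prevalence 30% (the lower end of 30–40%); 10% loss to follow-up; at least 10 events per variable for prognostic value and 20 for the model; three measurements without prior support.

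**1. The plan's sample sizes reproduce.**
- Prognostic value: 10 × 16 = 160 events; 160 / 0.30 / 0.90 = 592.6, stated as 593. Evaluable: about 533.
- Model: 20 × 16 = 320 events; 320 / 0.30 / 0.90 = 1185.2, stated as 1185. Evaluable: about 1066.
- Two such samples: 2 × 1185 = 2370, as stated.

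**2. Chance of at least one false positive among k null tests.** If independent, it is 1 − (1 − α)^k.

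| Null variables | α = 0.05 | α = 0.10 |
|---|---|---|
| 3 (MDTA, MMHA, TCA) | 1 − 0.95³ = 14.3% | 1 − 0.90³ = 27.1% |
| 14 (alternative count) | 1 − 0.95¹⁴ = 51.2% | 1 − 0.90¹⁴ = 77.1% |
| 16 | 1 − 0.95¹⁶ = 56.0% | 1 − 0.90¹⁶ = 81.5% |

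MDTA is numbered twice, as an angle and as a category. Counting it twice gives four null tests: 18.5% and 34.4%.

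**3. Correlated tests.** Several measurements describe the same structure. The correlations are assumed, since the article gives none. With all 16 null and equally correlated test statistics:

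| Correlation | α = 0.05 | α = 0.10 |
|---|---|---|
| 0.3 | 48% | 73% |
| 0.5 | 37% | 61% |
| 0.9 | 15% | 26% |

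**4. Adding the multivariable step.** No retention level is stated, so p < 0.05 is assumed. In 1000 simulated datasets (533 patients, 30% events, all 16 null, screen at 0.10, then multivariable logistic regression), at least one false factor survived in 55% with independent variables and in 26% with correlation 0.3. The second step lowers the rate but does not bring it near 5%.

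**5. What confirmation in the second sample would do.** A null factor passes the 0.10 screen and then reaches two-sided p < 0.05 in the same direction with probability 0.10 × 0.025 = 0.0025. For 16 independent null factors: 1 − (1 − 0.0025)^16 = 3.9%.

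**6. What confirmation would cost in power.** The standard error of the log OR per SD is approximately 1/√(n × 0.3 × 0.7), and the ORs are assumed.

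| OR per SD | Passes screen, n = 533 | Confirmed, n = 1066 | Both |
|---|---|---|---|
| 1.2 | ln 1.2 / SE = 1.93; 61% | 2.73; 78% | 0.61 × 0.78 = 48% |
| 1.3 | ln 1.3 / SE = 2.78; 87% | 3.93; 98% | 0.87 × 0.98 = 85% |

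**The case against.** The main objective, as stated under Prognostic model, is to build a risk assessment model. For prediction, family-wise control is not the usual criterion; events per variable, bootstrapping and temporal validation are. **This stands**, and it confines the point to the single-factor claims.

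The variables are not named from univariate tests alone: a multivariable regression follows. Other filters remove measurements with poor reliability, one of any collinear pair, and one of BMI and height. **This stands as description.** It makes the family smaller than 16 and the simple formula an upper case, but step 4 shows the regression does not remove the inflation.

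The PREDICT sample size section also drops any variable whose ICC with CAI is 0.70 or less. Read literally, a null variable would hardly pass. A weak but real factor would hardly pass either, and other sections select by significant correlation. The rule therefore cannot be relied on as error control.

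A reader might infer that the plan promises a 5% overall error rate and breaks it. It does not: 0.05 is a general per-test level. A reader might also take 56% or 81% as the expected rate. Those figures require every candidate to be null, whereas the article reports earlier evidence for all but three, and those three are the ones it describes as explored.

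Finally, a multiplicity policy may sit in an analysis plan not shown here. Its absence alone would be no finding. The point rests on what is written: the risk-factor label, two different levels, and a second sample given only a whole-model role.

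**Conclusion.** The point holds in limited form. Followed as written, the plan would name at least one false risk factor more often than its per-test level suggests. The chance is about 14% at 0.05 and 27% at 0.10 if only MDTA, MMHA and TCA are null and their tests independent. It rises to 56% and 81% if all 16 are null and independent, or 37% and 61% at an assumed correlation of 0.5. The true figure depends on how many candidates are null and how strongly they correlate, which the article cannot tell us.

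The documents do not support the stronger inference that the prediction model is invalid or that its variable selection must be redone. What is affected is the conclusion drawn under the first aim about individual factors. The article should also settle whether 0.05 or 0.10 defines a significant correlation.

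**What to change.** 1. In the abstract and in both sections on the prognostic value of variables, call the factors selected in the first sample candidate predictors from exploratory screening, and report them as ORs with confidence intervals.
2. State which level, 0.05 or 0.10, defines a significant correlation.
3. In the planned temporal validation sample, estimate the OR and confidence interval of each selected factor. Reserve the term risk factor for those associated there in the same direction, at two-sided p < 0.05.

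Model entry need not change and no further patients are needed; the work is wording plus one extra set of regressions on data already planned.

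The cost is that weaker real factors may not earn the label. Under the assumptions in step 6, an OR of 1.2 per SD earns it about 48% of the time and an OR of 1.3 about 85%. Both figures fall if the sample is reduced as variables drop out, which the plan allows.

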**Discussion:**

This study will develop the first large scale model for the risk at CAI after an ankle sprain combining radiographic and patient characteristics. With this risk assessment model, patients at risk for CAI may be identified and properly informed on the treatment options. Patients identified as being at risk, may receive more adequate follow-up and become eligible for early surgical stabilization. This prevents patients from experiencing unnecessary long-lasting complaints, increasing the success rate of conservative and surgical treatment.

**Trial registration:**

Retrospectively registered:

NCT02955485 [Registration date: 3–11-2016].

NTR6139 [Registration date: 3–1-2017].

## Background

Chronic ankle instability (CAI) is a worldwide common sports orthopaedic problem. It mainly results from a lateral ankle sprain, progressing in up to 30–40% of patients to CAI despite adequate initial treatment [1, 2]. It is mainly defined as persisting complaints of giving way, pain and recurrent ankle sprains for at least 12 months [3]. Patients with CAI are generally eligible for surgery, whereas in the Netherlands in case of acute ankle instability mainly only professional athletes qualify for surgical stabilization [4, 5].

Repeatedly spraining the ankle, as occurs in patients with CAI, can have serious consequences such as damage to the ankle joint and osteoarthritis on the long term [6]. When early surgical treatment is performed, it leads to better results compared to late surgical repair after both ruptures and ligament laxity [7]. However, currently it cannot be adequately assessed which patients will not respond to conservative treatment and will develop CAI directly after an ankle sprain.

To determine who is eligible for early surgical treatment the contributing risk of prognostic factors should be determined. Many prognostic and risk factors for ankle sprains and ankle instability have been studied. Kobayashi et al. [8] wrote a critical review in 2014 outlining the many neuromuscular factors that have been studied and whether they are correlated to ankle instability. They concluded it was difficult to compare the findings as there was a lack of standardization for inclusion. Other factors that have been studied on their potential contribution to ankle instability are factors such as patient characteristics [9, 10], foot and ankle configuration [11–15], joint pathology [16–18] and treatment [19–23].

A large amount of factors associated with ankle sprains are of neuromuscular origin. An adequate rehabilitation program may help prevent progression to chronicity [8]. Other factors, for example patient characteristics, foot and ankle configuration and joint pathology, are already present at time of the initial sprain. These factors will not be positively influenced by a functional training program in contrast to neuromuscular associated factors. A risk assessment model based on factors that cannot be changed by rehabilitation programs, using standardized inclusion criteria, may therefore provide a reliable risk analysis on the development of chronic complaints.

### Aim of the study

To identify which patient characteristics and joint geometric factors are associated with development of CAI after an ankle sprain and subsequently develop and validate a risk assessment model to indicate which patients are at risk for developing CAI.

## Methods/Design

### Study design

This level II observational prospective cohort study, executed in 4 different Dutch hospitals, will include all subsequent patients visiting the Emergency Department (ER) reporting for a first-time sustained ankle inversion injury. These patients will be asked to fill out a questionnaire at 2 weeks, 3-, 6- and 12 months after their ankle sprain of which only the 12 month follow-up questionnaire is mandatory to diagnose CAI.

The study design (Fig. 1) is in accordance to the principles of the Declaration of Helsinki (version 10, October 2013 by 64th WMA General Assembly, Fortaleza, Brazil) and in accordance with the Medical Research Involving Human Subjects Act of the Netherlands. The study is approved by the local institutional review board (IRB) of the Academic Medical Center (AMC) and Flevoziekenhuis (W16_258 # 16.303), the Slotervaart Medical Center (U/16.130/P1654) and the VU Medical Center (VUmc) (2016.541).

**Fig. 1 Fig1:**
[figure not shown]
Study outline. Abbreviations: ER: Emergency Department; T_0_: 1st baseline questionnaire; T_1_: 2nd questionnaire at 3 months; T_2_: 3rd questionnaire at 6 months; T3: 4th questionnaire at 12 months. Blue: Standard care at the ER; Red: Inclusion phase; Green: Included patients

### Study centres and participants

This study will be conducted at the ER of four Dutch hospitals: the AMC Amsterdam, Flevoziekenhuis Almere, Slotervaart Medical Center Amsterdam, VUmc Amsterdam. All subsequent patients that present themselves at the ER of one of the participating hospitals after an initial lateral ankle sprain will be treated according to standard protocol, including anamnesis, physical examination and (in case of positive Ottawa Ankle Rules (OAR)*) a radiograph [24]. When a mortise view and lateral radiograph is made and negative for ankle fractures or other joint pathology, patients are screened for eligibility according to the in -and exclusion criteria (Table 1).

**Table 1 Tab1:** Inclusion- and exclusion criteria

Inclusion criteria	Exclusion criteria
At least 16 years old	Present fracture or other joint pathology/bone matrix pathology
Visited the ER within one week after a lateral ankle sprain	A diagnosed OCD after primary inclusion
Agreed with being approached for this study	Medial ankle instability
Reported anterolateral ankle pain after an ankle sprain or ankle distortion	Previous ankle surgery
Filled out the baseline, 3-, or 6 month questionnaire; and the 12 month follow-up	An unreliable radiograph due to the angle in which it is made or low quality
	Acute surgical repair or the ATFL/CFL or any other form of surgery within 12 months after the ER visit

*Abbreviations*: *ER* Emergency Department, *AP* anteroposterior, *OCD* osteochondral defect, *ATFL* anterior talofibular ligament, *CFL* calcaneofibular ligament

*The OAR are a requirement at the ER according to Dutch protocols to conclude whether there is an indication for a radiograph. However, in cases of severe LAS patients there is a high risk at false positive OAR despite the absence of a fracture (due to a painful lateral malleolus with or without the ability to bear weight).

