### Definition CAI

Chronic ankle instability is defined as: *The perception of ‘giving-way’, in combination with a history of recurrent ankle sprains, the sensation of ankle instability and persistent disabilisty (pain, swelling* etc.*) that has not resolved in the time-frame from the first initial sprain up to the 12-months follow-up* [3, 25, 26]*.*

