#### Follow-up

A legally required waiting period of two weeks is observed prior to asking consent and sending the questionnaires to the patient’s home address or email address. Patients are asked to fill out the first questionnaire immediately which gives a T0 (baseline measure at approximately two weeks after the initial sprain). The subsequent evaluation time points are T1 interim evaluation after three months, T2 after six months, and T3 at twelve months. The questionnaires contain questions about patient characteristics, previous ankle sprains, treatment, restrictions and complaints. Additionally the questionnaires contains the Foot and Ankle Outcome Score (FAOS) and the Cumberland Ankle Instability Tool (CAIT) to evaluate recovery. To ensure all patients with CAI are identified, one year after their ER visit they will be contacted, inquiring on persisting complaints and ankle instability. Patients that indicate on the first questionnaire they sustained ankle sprains prior to their ER visit will not receive further follow-up questionnaires, as these patients are considered to have CAI and therefore need no extra monitoring to identify whether they develop CAI or not. They will not be included in the primary analysis as this may lead to overfitting of the current model. Concomitant neuromuscular adaptations and additionally may follow a different rehabilitation route due to familiarity with the complaints.

In case of persisting complaints six months after the ER visit, patients will be eligible for surgical treatment according to Dutch standards. This is to avoid unnecessary invasive treatment on patients as a large proportion recover by means of conservative treatment [7].

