### Adverse events

No study-related adverse events are expected as the study contains an observational cohort with 1 set of radiographs made according to standard protocol.

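### Excluding patients whose osteochondral defect is diagnosed after inclusion conditions the cohort on information unavailable at the ER, and probably, though not certainly, lowers predicted CAI risk

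*Protocol article*

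**What the plan says.** Under Study centres and participants, screening takes place "When a mortise view and lateral radiograph is made and negative for ankle fractures or other joint pathology". Table 1 then gives, among the exclusions, "A diagnosed OCD after primary inclusion". This line is separate from the exclusion for surgery within 12 months, so it also covers patients who are never operated on. It has no time limit, and the article describes no analysis that keeps these patients.

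The Background sets the moment of use. The stated gap is that at present "it cannot be adequately assessed which patients will not respond to conservative treatment and will develop CAI directly after an ankle sprain".

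The Adverse events section describes "1 set of radiographs made according to standard protocol", so the study itself plans no later imaging.

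The outcome at 12 months, under Definition CAI, is giving-way "in combination with a history of recurrent ankle sprains, the sensation of ankle instability and persistent" disability. Under Follow-up, "one year after their ER visit they will be contacted, inquiring on persisting complaints and ankle instability".

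**The concern.** A prognostic model should be developed and validated in everyone who would be eligible when the prediction is made. Here some patients are dropped because of what happens to them afterwards. A physician at the ER has a film that is negative for joint pathology and cannot know which patients will later be found to have an osteochondral defect (OCD). The exclusion cannot be applied at that point.

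If the later diagnosis is linked to the course of complaints, the exclusion also removes events and non-events unequally. A patient who keeps complaining is investigated, found to have a defect and dropped. A patient with the same lesion who recovers may never be imaged and stays in as a non-event. The intercept of the model would then be too low for the population seen at the ER. Temporal validation would look sound all the same, since Table 1 applies to the development and the validation set alike. The cut-offs that are to steer patients towards surgery, watchful waiting or no surgery rest on these predicted risks.

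**Working it through.** **The plan's own figure.** Events needed: 20 × 16 = 320. At 30% CAI: 320 × 3.33 = 1065.6, rounded up to 1066. With 10% loss: 1066 / 0.90 = 1184.4, rounded up to 1185. Two sets: 2 × 1185 = 2370. The stated sizes reproduce.

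**Inputs for the effect of the exclusion.**
- CAI risk p = 30% or 40% (Sample size calculation).
- q = share of CAI patients with a later OCD diagnosis; r = the same share among patients without CAI. The documents give neither, so both are assumptions shown over a range.

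**Formulas.**
- Risk among those retained = p(1−q) / [p(1−q) + (1−p)(1−r)]. Equivalently, the odds are multiplied by (1−q)/(1−r).
- CAI rate among those removed = pq / [pq + (1−p)r].

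Worked example, p = 0.30, q = 0.10, r = 0.02: retained risk = 0.27 / (0.27 + 0.686) = 28.2%; CAI rate among those removed = 0.03 / (0.03 + 0.014) = 68%.

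| q | r | CAI rate among removed (p = 30%) | Retained risk, p = 30% | Retained risk, p = 40% |
|---|---|---|---|---|
| 2% | 0.5% | 63% | 29.7% | 39.6% |
| 5% | 1% | 68% | 29.1% | 39.0% |
| 10% | 2% | 68% | 28.2% | 38.0% |
| 15% | 2% | 76% | 27.1% | 36.6% |
| 20% | 2% | 81% | 25.9% | 35.2% |
| 2% | 2% | 30% | 30.0% | 40.0% |
| 2% | 10% | 8% | 31.8% | 42.1% |

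The first five rows give a fall of 0.3 to 4.1 points at 30% and 0.4 to 4.8 points at 40%. The last two rows show no shift when q = r and a rise when q < r.

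**Same question, other inputs.** Let s be the share of all patients with a later OCD diagnosis and e their CAI rate. Observed prevalence = (0.30 − s·e)/(1 − s), and the share of events lost = s·e/0.30.
- s = 2%, e = 50%: 0.29/0.98 = 29.6%; 3.3% of events lost.
- s = 4%, e = 70%: 0.272/0.96 = 28.3%; 9.3% lost.
- s = 6%, e = 90%: 0.246/0.94 = 26.2%; 18% lost.

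At e = 30% the formula returns 30% for any s. The fall therefore needs a CAI rate above 30% among those removed.

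**Overlap with the surgery exclusion.** Patients operated on within 12 months leave the cohort anyway, and only the rest count against this criterion. If q = 10% and r = 2% include operated patients and half of each group was operated on, surgery alone takes the risk from 30% to 29.1% (q = 5%, r = 1%). The OCD criterion then takes it from 29.1% to 28.2%, about 0.9 points instead of 1.8.

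**Is the later diagnosis driven by complaints?** Two statements point that way. The single set of radiographs means that a later diagnosis normally has to come from work-up outside the study. The Discussion says that complaints are usually assumed to resolve after a sprain and that patients then drop out of physicians' sight. Recovered patients thus have little route to a diagnosis. This is an inference; no section says when, how or in whom an OCD is found.

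**The case against.** The strongest case on the other side has four parts.

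- **The direction is not documented.** A reader might infer that a later OCD is established to occur mainly in patients with persisting complaints, and that predicted risk is therefore shown to be too low. The documents do not support that. Persisting complaints are not yet CAI: the definition also demands giving-way, recurrent sprains and a sensation of instability, so a patient with an OCD and pain alone would be a non-event. Testing only high CAI rates among these patients builds the direction in. This stands, and it is why the direction is given only as probable.
- **Part of the effect belongs to the surgery exclusion.** This stands too. Shares that count every later OCD diagnosis overstate what this criterion does by itself, so the 18% of events lost is an upper-side figure even under its own assumptions.
- **The exclusion has a purpose.** Other joint pathology is excluded at entry, and CAI is ascertained by questionnaire and contact. Keeping these patients could count OCD complaints as CAI. The risk is real, but the definition already decides who is an event, and a sensitivity analysis without these patients shows how much depends on it.
- **The consequences are limited.** The smallest shifts are minor beside a planning range of 30–40%. Prevalence is also re-estimated at intervals from 500 to 2250 returned questionnaires, so lost events need not erode events per variable. This is fair as regards sample size. It does not restore a cohort that matches the patients seen at the ER.

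The line in Table 1 might also be meant for defects found on re-reading the ER film. The wording does not say so; if that is the intent, the change below states it.

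**Conclusion.** The concern stands in limited form. Certain from the text: ER-eligible patients leave both the development and the validation set on post-baseline information that no user can have at the ER, and no other section repairs this. That holds whichever way the bias runs.

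Probable only: predicted CAI risk is biased down. This rests on the inference that a later diagnosis follows continuing complaints, and on a CAI rate among the unoperated patients removed that exceeds the cohort rate. Under the assumed shares the fall is about 0.3 to 4 points at 30% risk and 0.4 to 5 points at 40%, and smaller where surgery already removes many of them. The documents fix neither the direction nor the size. The sample sizes of 1185 and 2370 are not in question.

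**What to change.** - Reword the Table 1 line so that the exclusion covers only an OCD visible or known at the ER visit.
- Keep patients with a later OCD diagnosis in the primary cohort and classify CAI at 12 months by the protocol's own definition.
- Record the later diagnosis as a follow-up finding, and report how many patients are affected and their CAI status.
- Give a sensitivity analysis without these patients.

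The cost is one line of Table 1 and one extra analysis. The 12-month questionnaire and contact already supply the outcome, so no visits are added, and 1185 and 2370 stay as they are. The drawback is that some events may reflect a coexisting OCD; the sensitivity analysis shows how far that matters.
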